### 2.3 Randomization and Blinding

Upon the completion of baseline assessments, patients are randomly assigned to either CARE, TARE, or AC in an equal allocation ratio (1:1:1) using a permuted-block design with varying block sizes. The randomization is stratified by menopausal status (premenopausal and postmenopausal) which is evaluated at time of diagnosis. A study biostatistician ([name]) prepares the randomization schema prior to trial start-up, and the randomization allocation is provided to staff *via* a web-based application (REDCap) (24), and study investigators are blinded to the randomization process. The intervention allocation is not blinded to the study participants, interventionists, and outcome assessors due to the nature of exercise intervention.

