### 2.9 Statistical Analysis

Initial descriptive analyses will be used to evaluate baseline comparability among the three intervention groups, using ANOVA, or Kruskal-Wallis tests for continuous variables and chi-square tests for categorical variables. Unless otherwise specified, Statistical testing will be conducted at a two-sided 0.05 alpha level to determine statistical significance. For our primary and secondary outcomes, the variables used for the primary analysis will be the 2- and 4-month measurements of trial outcomes assessed during and at the end of the intervention period. Linear mixed-effects models will be used with the longitudinal data for the between-group comparisons, where two indicator variables for the treatment group (TARE, AC) relative to CARE, the baseline value of the outcome, and an indicator variable for measurement time (2-month/4-month) will be included as fixed-effects and subjects as random-effects in the models. With Bonferroni correction applied, the Wald test will be performed at 0.025 two-sided alpha level for each of the two comparisons regarding treatment effects (i.e., CARE vs. TARE, and CARE vs. AC); the between-group differences will be reported with corresponding 0.975 two-sided confidence intervals. Significant group differences will be followed by stratified analyses within measurement time (two and four months), and testing of group-time interactions, to evaluate treatment group differences within measurement time.

Post-intervention outcomes will be evaluated using the same linear mixed-effects models. The dependent variables will be the 8- and 12-month post-intervention measures, with the 4-month post-intervention measure, included as a fixed-effect.

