The primary analysis would include all completed outcome assessments (regardless of whether the woman stayed on the intervention), inviting those who drop from the intervention to return for outcome assessments. The only missing data here would be those who drop the intervention and do not return for outcome assessments. Preliminary analyses will compare women who do and do not contribute to this analysis on baseline characteristics. Sensitivity/subgroup analyses will include (1): the receipt of chemotherapy as an established a-priori confounding factor due to possible chemotherapy-induced changes of chronic inflammation in adipose tissue (82–85), (2) multiple imputations of missing 2- and 4-month data (to evaluate the effect of missing data) (3); additional adjustment for baseline variables that differ between groups (to evaluate the effect of possible group differences on variables related to outcomes); and (4) adherence-based analysis, limiting subjects to those with at least 80% adherence (to estimate treatment effects under full adherence).

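### The primary model omits the stratification factor and receipt of chemotherapy, and one sensitivity analysis picks its covariates by chance baseline imbalance

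*Protocol article*

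**What the plan says.** Section 2.9 of the protocol article lists the terms of the primary linear mixed model. The fixed effects are "two indicator variables for the treatment group (TARE, AC) relative to CARE, the baseline value of the outcome", and then "an indicator variable for measurement time (2-month/4-month) will be included as fixed-effects and subjects as random-effects in the models". No other covariate is named.

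Section 2.3 states: "The randomization is stratified by menopausal status (premenopausal and postmenopausal"). No other stratification factor is given.

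Section 2.9 then lists four sensitivity/subgroup analyses. Item (1) concerns "the receipt of chemotherapy as an established a-priori confounding factor due to possible chemotherapy-induced changes of chronic inflammation in adipose tissue". Item (3) is "additional adjustment for baseline variables that differ between groups"; its stated purpose is to see what group differences on outcome-related variables do to the result.

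On baseline data the same section says: "Initial descriptive analyses will be used to evaluate baseline comparability among the three intervention groups, using ANOVA, or Kruskal-Wallis tests" for continuous variables, with chi-square tests for categorical ones. The default rule is that "Statistical testing will be conducted at a two-sided 0.05 alpha level to determine statistical significance".

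**The concern.** There are two separate weaknesses.

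First, two factors with a clear claim to a place in the primary model are not in it. Menopausal status was important enough to stratify on, and a stratified design is normally matched by an analysis that includes the stratum. Receipt of chemotherapy is complete before baseline and collected as treatment history (section 2.5.6). It varies between participants, since Table 1 admits women treated with chemotherapy and/or radiation. The plan itself ties it to adipose inflammation, the subject of the primary outcome. Leaving out a prognostic baseline factor wastes precision and gives up protection in the trials where that factor happens to fall unevenly.

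Second, item (3) lets observed difference between arms decide the covariates. Allocation is random, so a baseline difference is chance. It says nothing about whether the variable predicts the outcome, which is what makes adjustment worthwhile. The adjusted model cannot be written down until between-arm data have been seen.

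**Working it through.** **1. The plan's own figure.** Inputs from section 2.8: effect size 0.5, two-sided alpha 0.025, 80% power, 15% dropout.
- Normal approximation: n = 2(z₀.₉₈₇₅ + z₀.₈₀)²/d² = 2(2.2414 + 0.8416)²/0.25 = 76.04, so 77 per arm.
- Two-sample t-test solution: 77.3, so 78 per arm, as stated.
- Dropout: 78/(1 − 0.15) = 91.8, so 92, as stated.

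Both figures reproduce, and nothing below changes them.

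**2. Precision from adding chemotherapy.** Assumption, not in the documents: chemotherapy explains a share R² of the variance left in the model as listed. The residual SD is then multiplied by √(1 − R²).
- n per arm for 80% power = 76.04 × (1 − R²), rounded up.
- Power at 78 per arm = Φ(0.5·√(78/2)/√(1 − R²) − 2.2414). With R² = 0 this is Φ(3.1225 − 2.2414) = Φ(0.881) = 81.1%.
- Equivalent gain in sample size = 1/(1 − R²) − 1.

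| Assumed R² | n per arm for 80% power | Power at 78 | Equivalent gain in n |
|---|---|---|---|
| 0 | 77 | 81.1% | none |
| 0.02 | 75 | 81.9% | 2% |
| 0.05 | 73 | 83.2% | 5% |
| 0.10 | 69 | 85.3% | 11% |

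For R² of 0.02 to 0.10 the gain is therefore about 1 to 4 power points (81.9 − 81.1 = 0.8; 85.3 − 81.1 = 4.2). At R² = 0.20, beyond that range, power would be 89.4%.

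**3. Validity.** A simulation used three arms of 78, a single follow-up measure, independent randomisation and an assumed chemotherapy prevalence of 0.5. CARE vs. TARE was tested at two-sided 0.025, with 20,000 runs under no effect and 8,000 at d = 0.5. Results are for R² 0.05 / 0.10 / 0.20.

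| Strategy | Type I error | Power |
|---|---|---|
| Never adjust for chemotherapy | 0.024 / 0.026 / 0.025 | 80% / 80% / 81% |
| Adjust only if baseline chi-square p < 0.05 | 0.024 / 0.025 / 0.022 | 80% / 80% / 82% |
| Always adjust | 0.025 / 0.026 / 0.025 | 82% / 84% / 89% |

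- No strategy inflates the overall error rate.
- The imbalance rule picked chemotherapy in about 5% of runs, whatever its R². It therefore recovers almost none of the available power.
- Within that 5%, the unadjusted test rejected a true null in 2.8% / 5.2% / 7.3% of runs. The first value cannot be told from 2.5%: it rests on 0.0485 × 20,000 = 970 runs, with standard error √(0.0278 × 0.9722/970) = 0.5 points. The other two show the protection lost when chance imbalance meets a more strongly prognostic factor.

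**4. How often item (3) would find something.** This needs a reading that the article does not state, namely that a variable differs when p < 0.05. With k independent baseline variables, the chance of at least one flag under perfect randomisation is 1 − 0.95ᵏ: 40% for k = 10, 64% for 20 and 79% for 30. The values of k are also assumed.

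**5. Menopausal status.** No figure is put on this factor. Stratified blocks already balance it across arms. If it is prognostic and left out, its variance stays in the residual although the design has removed it from the between-arm difference. The test is then conservative, not liberal.

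**The case against.** The other side has a good deal to say.

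- The primary covariates are fixed in advance. A reader might infer that the trial's adjustment in general follows observed imbalance, but the documents do not support that. The rule belongs to one of four sensitivity/subgroup analyses, and the primary tests at 0.025 do not depend on it. This stands in full.
- Section 2.9 calls chemotherapy "the receipt of chemotherapy as an established a-priori confounding factor", so a reader might infer that leaving it out biases the primary result. It does not: chemotherapy precedes randomisation, so it cannot confound the randomised comparison on average, and step 3 shows nominal error rates without it. The word is loose. This too stands.
- Chemotherapy has its own pre-specified analysis, which may also address whether the effect differs by chemotherapy. A main-effect term would not answer that, so the analysis should stay. It does not give the primary contrast the precision.
- The baseline value of the outcome, measured after chemotherapy, may already absorb part of its effect. That is true, and it is why R² is an assumption about what remains.
- Item (3) states an aim concerning outcome-related variables, and the full protocol or SAP may hold a list. The absence of a list is therefore not the complaint. The stated rule is: it selects on difference, which does not serve that aim.
- The 40%, 64% and 79% might be read as error rates. They are only chances of a flag, under a threshold that the article never ties to item (3). The objection to selecting on difference does not need them.

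**Conclusion.** The point holds as a low-cost improvement in efficiency and pre-specification, not as a flaw in the primary inference. The primary model is pre-specified but leaves out the only stratification factor and a baseline factor that the plan itself considers relevant to the endpoint. Sensitivity analysis (3) selects covariates by a criterion unrelated to prognosis.

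The primary contrast is not biased, its overall type I error is not inflated, and 78 and 92 per group stand. The loss is about 1 to 4 power points at 78 per arm, if chemotherapy explains an assumed 2-10% of residual variance. Added to this are weaker protection in the few trials with a marked chance imbalance, and one supportive analysis whose model is unknown until the data are seen. The documents give neither the prevalence of chemotherapy nor its association with the outcome, so the size could lie outside that range.

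**What to change.** - Add menopausal status and receipt of chemotherapy as fixed effects in the primary mixed model. Keep the chemotherapy sensitivity/subgroup analysis.
- Report baseline characteristics by arm descriptively, without significance tests.
- Replace sensitivity analysis (3) with a covariate set named before any between-arm data are examined, chosen for relation to outcome and applied whatever the observed balance.

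The cost is a change of wording in the analysis section and one or two degrees of freedom in the primary model. No new data are needed, because menopausal status is recorded for stratification and chemotherapy as part of treatment history. The sample size and the alpha split stay as they are.

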#### 2.4.3 Attention-Control (AC)

Patients randomized to the AC group complete a 16-week home-based stretching program with the same stretches in the CARE and TARE groups at the end of their sessions. Minimal caloric expenditure is expected to be incurred as the stretches are low-intensity, low-impact, and low-volume. Participants are given an instructional booklet and trained in how to use the booklet to maximize the standardization of the home-based stretching (30) and increase compliance (31). Participants are also asked to complete weekly records detailing flexibility compliance and any physical activity performed outside of the study. At the end of the initial 16-week period, the AC group will be offered the 16-week CARE program weeks. Participants in the AC group who choose to perform the CARE program will complete one more assessment after the exercise program. Those who do not choose to partake in the CARE program will be finished with the study after the initial 16-week period.

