#### 2.5.5 Exercise Adherence

Exercise adherence is captured for the TARE and CARE groups by the following measures: 1) percentage and the number of prescribed sessions attended (out of 48 sessions); 2) average minutes of exercise/week (76). Participants are considered compliant if they attend ≥ 80% of the total prescribed number of exercise sessions and ≥ 80% of the total prescribed minutes/exercise sessions. Reasons for any missed sessions are documented throughout the study, and a make-up session can be scheduled as soon as possible with no more than three supervised sessions allowed per week. Participants have a two-week window post the 16-week intervention to make up for any missed sessions due to potential illness, family or work obligations, and COVID-19-related issues. Any sessions not completed within the 18-week period is not made up and counted as missed session.

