### 2.8 Sample Size

We anticipate recruiting 276 patients over a 48-month period and randomizing 92 patients to each arm of the study. Our hypotheses and analyses regarding our primary and secondary outcomes will reflect the comparison between CARE vs. TARE, and CARE vs. AC. Since the primary analysis involves two statistical comparisons, we will apply Bonferroni adjustment to control the overall type I error rate at 0.05 level. We estimated samples sizes for these two comparisons with each evaluated at two-sided alpha = 0.025. Our estimates of exercise intervention effect sizes were derived from randomized clinical trials (78–80) in addition to our preliminary data (81); most significantly, a study comparison of traditional endurance training vs. high-intensity circuit training (80) with effect sizes for outcomes common to our proposed trial (fat mass, lean body mass) was approximately 0.5-0.6. Effect sizes comparing exercise interventions to AC groups were larger, on 0.7-1.0. Our preliminary data compared exercise to AC (15 subjects per group), effect sizes were on the order of 1.0 (body composition measures) to 2.5-3.0 (inflammatory and other biomarkers) (81). The sample size determination was based on the comparison of the primary outcome between the CARE and TARE group because we expected that the difference between the CARE and AC group was larger than that between the CARE and TARE groups. We used an effect size of 0.5, two-sided alpha=0.025, and 80% power to estimate the sample size for comparisons of CARE vs. TARE, yielding a required 78 participants per group. To account for an anticipated 15% dropout rate, we will randomly assign 92 participants to each of the three groups. This will provide 80% or higher power to detect effect sizes of 0.5 and higher for other outcomes. For the optional biopsies, the sample size has been estimated at 50 participants per group based on our preliminary work (81). This will provide 80% power to detect a between-group difference, at a two-sided 0.025 alpha level, when the effect size is 0.9 for biopsy outcomes.

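### Sensitivity analysis (4) keeps only women with at least 80% adherence and is said to estimate effects under full adherence; a subset chosen after randomisation, on a criterion AC cannot share, does not estimate that

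*Protocol article*

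**What the plan says.** Section 2.9 introduces a list with "Sensitivity/subgroup analyses will include". Item (4) is an "adherence-based analysis, limiting subjects to those with at least 80% adherence (to estimate treatment effects under full adherence". The primary analysis is a different one: "The primary analysis would include all completed outcome assessments (regardless of whether the woman stayed on the intervention".

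The adherence rule is in Section 2.5.5. "Exercise adherence is captured for the TARE and CARE groups by the following measures", namely sessions attended out of 48 and average minutes per week. Women are "considered compliant if they attend ≥ 80% of the total prescribed number of exercise sessions and ≥ 80% of the total prescribed minutes/exercise sessions".

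The AC arm stretches at home (Section 2.4.3): "Participants are also asked to complete weekly records detailing flexibility compliance and any physical activity performed outside of the study". No cut-off is attached to those records.

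Section 2.8 says that the hypotheses and analyses for the primary and secondary outcomes "will reflect the comparison between CARE vs. TARE, and CARE vs. AC".

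**The concern.** The article fixes both a method and the quantity the method is meant to estimate, and the two do not match.

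- **Selection after randomisation.** Who reaches 80% is known only once the programme has run. Section 2.5.5 expects sessions to be missed for illness, family or work obligations and COVID-19. Illness, at least, could plausibly bear on inflammatory markers. Women who reach the threshold may therefore differ from those who do not in ways that affect the outcome, and randomisation no longer balances the groups compared.
- **No common criterion across arms.** CARE and TARE women are judged on supervised sessions and minutes. AC women can only be kept in full or filtered on home stretching.
- **80% is not full.** Even without selection, a subset whose members attend 80% or more describes that range of attendance, not complete attendance.

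At stake is how a secondary result is read. A difference in the adherent subset would carry the label of the effect under full adherence when part of it could be selection.

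**Working it through.** **1. The plan's own figures.** Section 2.8 uses effect size 0.5, two-sided alpha 0.025 and 80% power. A two-sample t-test needs 77.3 per group, rounded up to 78. Allowing for 15% dropout, 78 / 0.85 = 91.8, so 92. Both stated figures reproduce. The planned 78 evaluable women per arm is used below.

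**2. The threshold.** 0.80 x 48 = 38.4, so a woman needs at least 39 of 48 sessions, and also 80% of prescribed minutes. Section 2.4 gives about 60 minutes per session for both programmes, while Section 2.4.2 gives about 80 for TARE. The minutes criterion depends on which applies, so those statements must be reconciled.

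**3. What restriction does when exercise has no effect (CARE restricted, AC not).** Let p be the adherent share in CARE and g the gap in mean outcome, in SD units, between adherers and non-adherers. With no effect, the whole CARE arm has the same expected mean as AC; set it to 0. Then p x (adherer mean) + (1 - p) x (adherer mean - g) = 0, so

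adherer mean = (1 - p) x g.

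The documents give neither p nor g. Assumed values:

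| p | g = 0.2 | g = 0.4 | g = 0.6 |
|---|---|---|---|
| 0.85 | 0.03 | 0.06 | 0.09 |
| 0.75 | 0.05 | 0.10 | 0.15 |
| 0.60 | 0.08 | 0.16 | 0.24 |

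The middle cell is 0.25 x 0.4 = 0.10 SD, one fifth of the planning effect of 0.5. The sign follows g: positive if adherers would have done better anyway, negative if worse.

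A second selection model treats adherence and outcome as bivariate normal with correlation 0.2-0.5 and 60-80% adherent. It gives 0.07-0.32 SD. The order of magnitude is similar, and the inputs are again assumed.

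**4. Rejection rates, as an illustration only.** A two-sample t-test at 0.025 with 78p women against 78 rejects in 2.7% (p = 0.85, g = 0.2), 5.0% (0.75, 0.4) and 17% (0.60, 0.6) of trials with no effect. With the 50 per group planned for the optional biopsies, the same three cases give about 2.65%, 4.1% and 11%. These ignore the baseline adjustment and the two time points in the Section 2.9 model, and no decision rule is tied to item (4).

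**5. CARE vs TARE.** Here the rule exists in both arms. With a common gap, the spurious difference is g x [(1 - p for CARE) - (1 - p for TARE)]. Equal shares and gaps cancel. At 60% against 80%, it is 0.20 x g, or 0.04-0.12 SD for g of 0.2-0.6. Nothing guarantees equality: Section 3 notes that intensity is pre-specified in CARE but varies by individual in TARE.

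**The case against.** The strongest reply is that this is one item in a list of sensitivity analyses, beside a primary analysis that keeps every completed assessment whatever the adherence and invites women who drop the intervention back for measurement. Item (2) adds multiple imputation. A prespecified adherence subset is common and is read as supportive. This stands, and it limits the weight of the point. It does not rescue the stated purpose, which is wrong whatever the rank of the analysis.

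Second, a reader might infer that adherence is recorded in the exercise arms alone, and hence that CARE vs AC must become selected CARE women against all AC women. The documents do not support that. Section 2.4.3 has AC women log stretching compliance, and item (4) does not exempt AC. An unseen analysis plan could set an AC cut-off, so its absence from the article is not itself the fault. The fault that remains is that a cut-off on home stretching would select on a different behaviour from attending supervised training, so supplying one would not make the arms comparable.

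Third, the illustrative figures rest on assumed inputs, and the low end is negligible. The Section 2.9 model adjusts for the baseline outcome, so only the gap remaining after adjustment matters. This also stands. The figures show what could happen; they do not forecast it.

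**Conclusion.** The point holds as a mismatch between method and stated purpose in a secondary analysis. Restricting to women with at least 80% adherence does not estimate treatment effects under full adherence, and for CARE vs AC the two arms cannot be selected on the same criterion. No analysis-plan detail would cure this while the subset keeps that label.

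Two stronger readings should be resisted. The trial's main result is not compromised, because the primary analysis does not condition on adherence. Nor do the documents show that the subset will favour CARE: that requires adherers to do better on these outcomes regardless of exercise, which is plausible but nowhere stated. If AC is left unrestricted, an illustrative bias is 0.03-0.24 SD, assuming 60-85% adherence and a residual gap of 0.2-0.6 SD. If AC is also filtered on its logs, that calculation no longer applies and the net bias could be smaller or of either sign. The correction is worth making because it is cheap and prevents a secondary result from being misdescribed.

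**What to change.** 1. In Section 2.9, delete the statement that the subset estimates effects under full adherence. Label it descriptive and state how AC women are handled in it.
2. If an adherence effect is wanted, keep all randomised women with outcome data.
   - **CARE vs AC:** use randomisation as the instrument for CARE sessions attended during the 16 weeks (two-stage least squares). AC women have zero, since Section 2.4.3 offers them CARE only afterwards. State the exclusion assumption (assignment acts on the outcome only through sessions attended) and the linear-dose assumption. Do not dichotomise at 80%, because that would treat attendance below the cut as no exposure.
   - **CARE vs TARE:** use inverse-probability-of-adherence weights built from the baseline covariates already collected (Section 2.5.6). Say that the target is attendance at or above the threshold, and state the assumption of no unmeasured confounding.

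The cost is plan wording and modest programming, with no change to conduct or data collection. Intervals will be wider, and the results will rest on assumptions that must be reported with them.
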